### Aims

The principal objective of this study is to evaluate, in nonabstinent patients with AUD, the efficacy of 1 week of tDCS (five consecutive twice-daily sessions) versus placebo in reducing alcohol consumption within the 24 weeks following the treatment. The hypothesis is that tDCS, by inducing changes in the neuronal activity of the DLFPC to decrease the craving, can lead to a decrease in the consumptions of alcohol in patients suffering from AUD.

In addition, we will assess the effects of tDCS on mood, cognitive behavior, and quality of life and, in participants who have AUD combined with tobacco use disorder (TUD), the effect of tDCS on tobacco craving and consumption.

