### Outcomes

In the “*Guideline on the development of medicinal products for the treatment of alcohol dependence,*” for an alcohol reduction strategy, the European Medicines Agency (EMA) recommend using a co-primary efficacy outcome, the change from baseline in total alcohol consumption (TAC) per month and a reduction in the number of heavy drinking days (HDD) [1]. Thus, our principal effective criteria on alcohol reduction will be both the change in TAC from baseline to week 24, defined as mean daily alcohol consumption over 28 days (in g/day), and the number of HDD, defined as more than 60 grams of pure alcohol in men and 40 grams in women consumed in one day. Baseline will be defined as alcohol consumption during the 28 days before randomization using the alcohol TLFB method, a validated method that retrospectively obtains estimates of daily drinking using a calendar [40, 41].

The secondary evaluation criteria will be the change from baseline to the end of the tDCS cessions and, then, for each 4-week period after the treatment up to week 24 in the following parameters:TAC (g/day) and number of HDDProportion of subjects with a significant categorical shift in World Health Organization (WHO) risk levels of drinking: low risk (*H* ≤ 40 g/d; *F* ≤ 20 g/d), medium risk (*H* ≤ 60 g/d; *F* ≤ 40 g/d), high risk (*H* ≤ 100 g/d; *F* ≤ 60 g/d, and very high risk (*H* > 100 g/d; *F* > 60 g/d) [38]Proportion of subjects with a 50 %, 70 %, and 90 % reduction in alcohol consumption, as well as, the proportion of patients who potentially achieve abstinenceLevel of alcohol dependence severity (alcohol dependence scale)Craving/urge to drink assessment (visual analog scale, obsessive compulsive drinking scale)Clinical global impression—severity and improvementScores for depression scales (Hamilton depression rating scale—17 items)Quality of life (short form health survey—12 items)

Other secondary evaluation criteria will include the change from baseline at week 4, week 12, and week 24 after the treatment, in the following:Biochemical alcohol consumption markers (gamma glutamyl transferase, mean corpuscular volume, aspartate aminotransferase, alanine aminotransferase, and carbohydrate deficient transferrin)Cognitive assessment (Montreal cognitive assessment)Number of cigarettes smoked/day and craving for tobacco (visual analog scale, tobacco-craving questionnaire) for smokers.

The number of patients with adverse events will be determined at the time of each visit.

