### Statistical analysis

All randomized patients will be used for the efficacy analyses. The baseline and demographic characteristics of the two groups (active tDCS vs placebo tDCS) will be recorded. Qualitative variables will be described in terms of numbers and percentages, and quantitative variables, in terms of means and standard deviations or medians and interquartile intervals. The co-primary outcome of change in TAC from baseline and reduction in the number of HDD at 6 months after treatment and its association with tDCS will be analyzed under the intention-to-treat principle using mixed model repeated measures (eight times).

The comparability of the two groups at baseline will be evaluated using the chi square test or Fisher’s test for qualitative variables, and Student’s T test or the Mann Whitney test for continuous variables. Then, a mixed model repeated measures will be conducted to estimate the effect of treatment on the TAC first, and HDD second. Observed cases will be considered random effects, and the site, sex, time, and treatment as the fixed effects. We will use multiple imputation techniques to compensate for any potential bias introduced by missing endpoint data [42].

For the primary outcome, per-protocol analysis will also be conducted among the participants who have completed baseline and endpoint assessments. The secondary outcome measurements will be analyzed with similar models to those used for the co-primary, continuous variables, and logistic regression, for dichotomized outcomes.

All tests will be one-sided. The primary results will be examined at a significance level of 0.0125 (co-primary outcome). For secondary outcomes, the threshold for significance will be fixed at 0.025. All analyses will be performed using SAS version 9.3 (SAS Institute, Inc, Cary, NC, USA) by the team of statisticians of the Unité de Soutien Méthodologique, Direction of Clinical Research, University Hospital of Dijon, France.

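### The blanket one-sided rule suits the two drinking outcomes but not the secondary outcomes framed without direction, nor the baseline comparisons

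*Protocol article*

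**What the plan says.** In the protocol article, the last paragraph of Statistical analysis opens with "All tests will be one-sided". It then sets 0.0125 for each primary outcome and adds "For secondary outcomes, the threshold for significance will be fixed at 0.025". No exception is made, and no direction is named for any outcome.

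The paragraphs before it list the tests. Baseline comparability uses the "chi square test or Fisher’s test for qualitative variables, and Student’s T test or the Mann Whitney test for continuous variables". Secondary outcomes are to be "analyzed with similar models to those used for the co-primary, continuous variables, and logistic regression, for dichotomized outcomes".

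The Aims section gives the main hypothesis a direction, namely that stimulation lowers alcohol consumption. The further aims have none: "we will assess the effects of tDCS on mood, cognitive behavior, and quality of life", and likewise the effect on tobacco craving and consumption in participants who also have tobacco use disorder. The Outcomes section turns these into secondary outcomes: the Hamilton depression scale, the SF-12, the Montreal cognitive assessment, cigarettes per day and tobacco craving.

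**The concern.** A one-sided test puts its whole error rate in one tail. For TAC and HDD that matches the stated hypothesis. For mood, cognition, quality of life and smoking the protocol asks what the effect is, and a one-sided test for benefit addresses only half of that question. If depression scores rose or cognitive scores fell under active stimulation, the planned test could only return a non-significant result. The Background calls most previous brain-stimulation studies preliminary, small and without follow-up, so the documents give little ground for ruling out an unfavourable effect in advance.

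The rule also reaches the baseline comparisons if read as written. Between randomised arms there is no favoured direction of imbalance, so a one-sided p-value there has no sensible interpretation, and the Pearson chi-square statistic carries no direction at all.

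**Working it through.** **1. Is the one-sided level built into the design?**

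Inputs from Sample size calculation: difference 10 g/day, SD 30 g/day, correlation 0.7, significance level 1.25 %, power 80 %, 274 patients before a 20 % allowance for drop-out, 340 in all. The number of repeated measures *m* behind the calculation is not stated, so it is an assumption here.

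For the mean of *m* equally correlated values, the variance factor is (1 + (m − 1) × 0.7)/m. With m = 3 this is 2.4/3 = 0.8, so the variance is 900 × 0.8 = 720.

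n per arm = 2 × (2.2414 + 0.8416)² × 720 / 10² = 14.4 × 9.505 = 136.9, so 137 per arm and **274** in all. (m = 4 gives 266; m = 8 gives 254.) Drop-out: 274/0.8 = 342.5, close to the stated 340.

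So 274 is consistent with a one-sided 0.0125 for each of two outcomes, which sums to 2 × 0.0125 = 0.025 one-sided. For TAC and HDD the one-sided choice is coherent.

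**2. What happens to a secondary outcome that truly worsens?**

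The documents give no planning effect for these outcomes, so a range of 0.2, 0.33 (one third) and 0.5 SD is assumed, with 137 per arm and a simple two-group comparison. Non-centrality is d × √(137/2) = d × 8.276.

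- Two-sided 0.05, probability of declaring the worsening: Φ(8.276 d − 1.960)
- One-sided 0.025 for benefit, probability of rejecting: Φ(−8.276 d − 1.960)

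| Assumed worsening | Non-centrality | Two-sided 0.05 declares worsening | One-sided 0.025 rejects |
|---|---|---|---|
| 0.2 SD | 1.655 | 0.38 | 0.00015 |
| 0.33 SD | 2.759 | 0.79 | 0.000001 |
| 0.5 SD | 4.138 | 0.985 | below 0.000001 |

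The rejections in the last column would wrongly indicate benefit, so the chance that the one-sided test declares the worsening is zero. The tobacco outcomes concern smokers only. Their numbers per arm are smaller and the two-sided probabilities correspondingly lower.

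**3. What does two-sided testing cost?**

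- Secondary outcomes: one-sided 0.025 and two-sided 0.05 share the critical value 1.960.
- Primary outcomes: one-sided 0.0125 and two-sided 0.025 share the critical value 2.241.

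The hurdle for benefit is therefore unchanged, and 274 and 340 stand. Two-sided testing at the printed 0.0125 would not be free. With m = 3 it needs 322 evaluable patients (322/0.8 = 402.5, so 403 randomised), or leaves 72 % power with 137 per arm.

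**The case against.** The best defence is that the sentence stands in a paragraph that sets thresholds only for primary and secondary outcomes, so it may not be meant for the baseline tests, and no decision in the article hangs on a baseline p-value. The direction of each test may also be given in a document not shown, and some secondary outcomes are described elsewhere in the article as hoped-for improvements. These arguments lessen the consequence, but they do not remove an unqualified rule covering every test, or its mismatch with aims worded without direction.

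Four stronger readings are tempting, and the documents do not support them:

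- *That several of the named tests have no one-sided form.* Student's t, Mann-Whitney, Fisher on a 2×2 table, and the treatment contrast in a mixed or logistic model all have one. Only the Pearson chi-square, and Fisher on larger tables, are non-directional, and even a 2×2 chi-square can be given a sign through its root.
- *That prescribed safety tests cannot be run.* None is prescribed. Outcomes says only that "The number of patients with adverse events will be determined at the time of each visit".
- *That harm would be hidden.* Only the formal declaration is lost. Group estimates and adverse event counts would still show a worsening.
- *That false claims of benefit become more likely.* The one-sided levels have the same critical values as the usual two-sided ones.

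**Conclusion.** The point holds in a limited form. The rule is sound for TAC and HDD, apart from the unstated direction. It does not suit mood, cognition, quality of life and tobacco outcomes, and it has no meaning for baseline comparisons. If the alternative is benefit, formal detection of a worsening falls from about 0.38, 0.79 or 0.985 to zero. Those figures rest on assumed effects of 0.2, 0.33 and 0.5 SD, about 137 patients per arm and the assumed direction of the test. Efficacy inference is not affected. This should be corrected because it governs how named outcomes are reported and the correction is free, but it does not threaten the primary result.

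**What to change.** Replace the blanket sentence with three statements:

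1. Secondary outcomes are tested two-sided at 0.05, with 95 % confidence intervals.
2. TAC and HDD are each tested either two-sided at 0.025, or one-sided at 0.0125 with the alternative stated as a greater reduction under active stimulation. The printed 0.0125 should not be relabelled as two-sided, since that would raise the required number of patients.
3. Baseline characteristics are described by arm, without one-sided tests.

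The cost is wording only. The critical values for benefit (2.241 and 1.960), the 340 patients and the power for efficacy all stay as they are.

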### Sample size calculation

As the primary efficacy outcome, the EMA recommends using both TAC and the number of HDD [1]. Besides, any reduction in total alcohol consumption of at least 10 g/day for patients with alcohol use disorders will reduce the annual and lifetime risk of alcohol-related death [3].

In this context, a sample size calculation based on an expected difference between the treatment groups of 10 g/day in total alcohol consumption, with a standard deviation for the TAC of 30 g/day and with an autocorrelation of 0.7 between observations in the same subject, indicates that 274 patients would be required.

By considering a significance level of 1.25 % (co-primary outcome), a power of 80 %, and with the hypothesis of a premature drop-out or a noninitiation of the treatment (acute repeated alcoholism) for 20 % of the patients, 340 patients (170 per group) should be included to meet the objectives of the study.

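### TAC and HDD are labelled co-primary, but alpha is halved as for an either-or claim, so the success rule is unsettled and the stated 80% power covers TAC alone

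*Protocol article*

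**What the plan says.** - **Endpoints.** The Outcomes section follows a regulatory guideline that, as the article describes it, recommends a co-primary outcome: "Thus, our principal effective criteria on alcohol reduction will be both the change in TAC from baseline to week 24", together with the number of HDD. The Sample size calculation section repeats the basis: "As the primary efficacy outcome, the EMA recommends using both TAC and the number of HDD".
- **Level.** The Sample size calculation section has "By considering a significance level of 1.25 % (co-primary outcome), a power of 80" percent. The Statistical analysis section has "The primary results will be examined at a significance level of 0.0125 (co-primary outcome"). The parenthesis is the only reason given for the level in either place.
- **Sidedness and secondary level.** "All tests will be one-sided", and "For secondary outcomes, the threshold for significance will be fixed at 0.025".
- **Power inputs.** The sample size rests on an "expected difference between the treatment groups of 10 g/day in total alcohol consumption" and a TAC standard deviation of 30 g/day. No effect, standard deviation or correlation is given for HDD.
- **Order.** The mixed model is fitted "to estimate the effect of treatment on the TAC first, and HDD second". No testing rule is attached to that order.
- **Secondary list.** The Outcomes section also lists TAC and HDD as secondary outcomes for every 4-week period through week 24.

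**The concern.** The label and the alpha point to different success rules. Co-primary endpoints, adopted as a pair and introduced with *both*, suggest that the trial succeeds only if each is significant. A level halved for two endpoints is the usual protection when significance on one of them is enough. The article does not say which rule applies.

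Three things follow:

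- The trial-level verdict is open for a plausible result. With TAC p = 0.01 and HDD p = 0.02, the trial fails if both are required at 0.0125, succeeds if either suffices at 0.0125, and succeeds if both are required at 0.025.
- The stated 80% is not the probability that the trial succeeds under either rule.
- The last 4-week period in the secondary list is the primary time point. The same comparison with p = 0.02 misses the primary threshold and meets the secondary one.

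**Working it through.** **1. Where 0.0125 comes from.** The one-sided secondary level is 0.025, and 0.025 / 2 = 0.0125. The article does not show this step. It is inferred from the two levels and the two endpoints.

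**2. Type I error under each rule.**
- Either suffices, each at 0.0125: at most 0.0125 + 0.0125 = 0.025.
- Both required, each at level a: a false claim needs rejection of at least one true null, so the error is at most a. This gives at most 0.0125 with the split and at most 0.025 without it. The split is not needed for this rule.

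**3. Reproducing the 274.** Inputs from the Sample size calculation section: difference 10 g/day, SD 30 g/day, autocorrelation 0.7, level 0.0125, power 80%. One-sided testing is from the Statistical analysis section.
- Per arm before the repeated-measures factor: 2 × [30 × (2.2414 + 0.8416) / 10]² = 171.1.
- Repeated-measures factor (1 + (m − 1) × 0.7) / m. The number of measurements m is not stated with the sample size. With m = 3 the factor is 2.4 / 3 = 0.80.
- 171.1 × 0.80 = 136.9, so 137 per arm and 274 in total, an exact match. Other choices: m = 1 gives 344, m = 4 gives 266, m = 8 gives 254, and two-sided 0.0125 with m = 3 gives 322.
- Drop-out: 274 / 0.80 = 343, against the stated 340. This is close enough.

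The 274 is therefore a TAC-only figure: 80% marginal power for TAC at one-sided 0.0125.

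**4. What follows without any HDD assumption.** The probability that both tests succeed cannot exceed that of TAC alone, so 80% is an upper bound if both are required at 0.0125. The probability that at least one succeeds cannot be below that of TAC alone, so 80% is a lower bound if either suffices.

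**5. Size, with HDD assumptions.** Assume HDD has the same power as TAC, and let r be the correlation between the two test statistics (bivariate normal). Each non-centrality is 2.2414 + 0.8416 = 3.083, so marginal power at 0.025 is Φ(3.083 − 1.960) = 0.87.

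| Rule | r = 0 | r = 0.5 | r = 0.8 |
|---|---|---|---|
| Both, each at 0.0125 | 64% | 69% | 73% |
| Both, each at 0.025 | 76% | 79% | 82% |
| Either, each at 0.0125 | 96% | 91% | 87% |

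Check at r = 0: 0.80² = 0.64; 0.8696² = 0.756; 1 − 0.20² = 0.96.

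If HDD had only 60% power at 0.0125, requiring both at that level would give 48% (r = 0) to 58% (r = 0.8).

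**6. Sample size for 80% joint power, equal effects, r from 0 to 0.8.** At 0.0125 each, 352 down to 316 evaluable patients. At 0.025 each, 298 down to 264. The plan has 274.

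**The case against.** The strongest reply is that the article is coherent if *co-primary* is used loosely. *Both* may only list two primary variables, and a Bonferroni split from one-sided 0.025 is then a valid design with at least 80% power. A condensed article may also leave the decision sentence to the full protocol or the analysis plan. Part of this stands: either-or with the split is a legitimate design, and a missing sentence alone would be no finding. But the article itself fixes the label, the level and the power, and its only reason for the halved level is a label that, in its usual sense, calls for no halving. That is a conflict between stated elements.

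A reader might infer more than the text supports:

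- *That type I error is inflated.* It is not, under either rule.
- *That fitting TAC before HDD sets up a third, fixed-sequence rule.* The wording gives an order of analysis and no gatekeeping.
- *That the trial is underpowered.* This holds only if both are required, and the size of the shortfall depends on HDD inputs that the article does not give. The article presents the 80% on TAC inputs and does not claim joint power.
- *That a secondary p = 0.02 could rescue a failed primary.* The primary threshold is fixed in advance. The overlap is a duplication that invites confusion, and no more.

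**Conclusion.** The point holds as a conflict between label and alpha that leaves the success rule unsettled. It is not a failure of error control, and the arithmetic behind 274 and 340 is not at fault. What rests on the article alone is that the split does not fit a both-required rule, that the verdict is open when only one endpoint reaches 0.0125, that 80% is a bound on trial power (upper or lower, depending on the rule), and that week-24 TAC and HDD are held to two thresholds.

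The power ranges in the table are illustrations. They assume equal power for HDD and a correlation of 0 to 0.8. Reading the 274 as exactly 80% TAC power also assumes three correlated measurements. Severity: should-fix.

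**What to change.** In keeping with the *both* wording, state that the trial is positive only if TAC and HDD at week 24 both favour active tDCS, each at one-sided 0.025. Replace the 0.0125 in the Sample size calculation and Statistical analysis sections accordingly. On the equal-power assumption this raises joint power from 64–73% to 76–82% with no added patients. The price is that a win on one endpoint alone is no longer a claim.

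If an either-or claim was intended, keep 0.0125, replace the co-primary *both* wording with multiple primary endpoints, and say that one significant endpoint suffices.

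In either case:
- State that the 80% refers to TAC alone, or give trial-level power with explicit assumptions for the HDD effect, its SD and its correlation with TAC.
- Remove week-24 TAC and HDD from the secondary list. The earlier 4-week periods can stay.

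The cost is wording in three sections, plus HDD assumptions if trial-level power is reported. The rule should be settled before unblinding.

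### Testing TAC and HDD each at a fixed one-sided 0.0125 is valid but needlessly strict: a better rule at the same inferred overall 0.025 exists whichever way success is defined

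*Protocol article*

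**What the plan says.** The Outcomes section of the protocol article names two principal criteria: "our principal effective criteria on alcohol reduction will be both the change in TAC from baseline to week 24", together with the number of HDD. It bases this on a regulatory guideline. It does not say whether one significant endpoint is enough or both are needed.

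The Statistical analysis section fixes the tests: "All tests will be one-sided", and "The primary results will be examined at a significance level of 0.0125 (co-primary outcome"). For secondary outcomes it says: "For secondary outcomes, the threshold for significance will be fixed at 0.025". The mixed model is to "estimate the effect of treatment on the TAC first, and HDD second". That sets the order of the two analyses; no significance level is passed from one test to the other.

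The Sample size calculation section uses the same level: "By considering a significance level of 1.25 % (co-primary outcome), a power of 80" per cent. The calculation is for TAC only, with an "expected difference between the treatment groups of 10 g/day in total alcohol consumption". It gives no effect size, standard deviation or power for HDD.

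**The concern.** Each primary p-value is compared with 0.0125 whatever the other test shows. Two tests at 0.0125 use up 0.025. Once one endpoint is significant at 0.0125, the other can be tested at the full 0.025 without raising the family-wise error above 0.025. The plan does not use this.

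Take TAC p = 0.005 and HDD p = 0.018. The plan would report HDD as not significant, although a valid procedure at the same overall level declares both. The protocol cites its guideline as recommending both measures, and joint success is where the flat rule loses most. The choice has to be fixed in advance, because it cannot credibly be made once the results are known. The article reports two participants enrolled at submission.

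**Working it through.** **Inputs from the protocol.** One-sided tests; 0.0125 for each of two endpoints; TAC difference 10 g/day, SD 30 g/day, within-subject autocorrelation 0.7; power 80%; 274 patients before and 340 after 20% drop-out.

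**Inputs not in the protocol (assumptions).** Overall level for the two primary tests: 2 × 0.0125 = 0.025, in line with the secondary threshold. HDD power at 0.0125: 80%, then 60%. Correlation r between the TAC and HDD test statistics: 0 to 0.9. The protocol's 0.7 links repeated measurements in one subject and says nothing about r.

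**The plan's own figure.** For the mean of m equally correlated measurements, the variance is 30² × (1 + (m − 1) × 0.7)/m, and n per arm = 2 × variance × (z₀.₉₈₇₅ + z₀.₈₀)²/10².
- m = 3: variance = 900 × 2.4/3 = 720; n = 2 × 720 × (2.2414 + 0.8416)²/100 = 136.9, so 137 per arm and 274 in total. This matches exactly, but m = 3 is inferred.
- m = 1 gives 344 and m = 8 gives 254.
- Drop-out: 274/0.8 = 342.5, against the stated 340.

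The stated size therefore fits one-sided 0.0125 and 80% power for TAC.

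**The three rules.** Let c₁ = z₀.₉₈₇₅ = 2.2414 and c₂ = z₀.₉₇₅ = 1.9600.
- Flat: an endpoint is significant if its statistic is at least c₁.
- Holm: the larger statistic must reach c₁; if it does, the other need only reach c₂.
- Both required: each statistic must reach c₂, with no split.

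Holm's gain for TAC is P(c₂ ≤ Z_TAC < c₁ and Z_HDD ≥ c₁), and the same with the roles exchanged for HDD. The gain for showing both is the sum of the two. Holm's first step is the flat rule's own criterion for at least one significant result, so that probability is identical under the two.

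**Results, both endpoints at 80% power at 0.0125.** The mean of each statistic is 2.2414 + 0.8416 = 3.0830; probabilities are bivariate normal.

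| r | Per endpoint: flat → Holm | Both: flat → Holm | Both, each at 0.025 |
|---|---|---|---|
| 0 | 80.0 → 85.5% | 64.0 → 75.1% | 75.6% |
| 0.5 | 80.0 → 84.6% | 68.7 → 77.8% | 78.6% |
| 0.7 | 80.0 → 84.1% | 71.3 → 79.4% | 80.4% |
| 0.9 | 80.0 → 83.2% | 75.0 → 81.5% | 83.2% |

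Simulation with 2 million draws at r = 0.5 and 0.7 agrees. At r = 0.7 the chance of at least one significant endpoint is 88.7% under both the flat rule and Holm.

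**HDD power 60%, r = 0.7.** TAC 80.0 → 81.9% (+1.9); HDD 60.0 → 68.1% (+8.1); both 56.5 → 66.5% (+10.0). Testing each at 0.025 gives 67.5% for both.

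**All 170 per arm informative (m = 3), r = 0.7, HDD power equal to TAC power.** Power at 0.0125 is 88.4%. Holm adds 3.0 points per endpoint and 6.0 for both.

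**Error rate.** With no effect on either endpoint, the family-wise error is the same under the flat rule and Holm: 0.0248 at r = 0 and 0.0181 at r = 0.9. With no effect on one endpoint and a very large effect on the other, the false-positive rate is 0.0125 under the flat rule and 0.025 under Holm. Neither exceeds 0.025.

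**The case against.** The strongest defence is that nothing here is wrong. Two tests at 0.0125 are a standard way to control the error rate, design and analysis use the same level, and the planned TAC power is met as designed. A reader might infer that the plan inflates the error rate or leaves TAC underpowered at 0.0125. The documents support neither. This defence stands, and it makes the point an efficiency improvement.

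A reader might also infer a fixed loss of about 4 points per endpoint and 8 for both. Those figures need r near 0.7 and 80% power for HDD, and the protocol gives neither. Borrowing its autocorrelation of 0.7 for r would be a mistake. With weaker HDD power the gain is very uneven between the endpoints. Only a range can be defended.

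Nor is Holm the answer in every case. The wording of the Outcomes section can be read as requiring both endpoints. Then each may be tested at 0.025, and Holm is itself slightly too strict: two p-values of 0.020 would pass a valid both-required test but fail Holm. So the success rule has to be settled first.

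Finally, the flat split gives simple simultaneous confidence bounds. Under Holm, if only one endpoint is significant, its compatible one-sided bound stays at zero effect, whereas the flat split keeps an informative bound. That is a real cost, because the protocol ties relevance to 10 g/day. It stands as the price of the change.

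**Conclusion.** The flat rule is valid but dominated in power. Every pair of p-values that succeeds under it also succeeds under Holm and, if both endpoints are required, under unsplit tests at 0.025. That much needs no assumption about effects or correlation, only that the intended overall level is 0.025.

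The size of the gain does rest on assumptions. With 80% power for each endpoint and r from 0 to 0.9, Holm adds 5.5 down to 3.2 points per endpoint and 11.1 down to 6.5 for both. With HDD at 60% and r = 0.7, the gains are 1.9, 8.1 and 10.0 points for TAC, HDD and both. If both must be significant, unsplit testing does slightly better than Holm: 80.4% against 79.4% at r = 0.7 with 80% power each.

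This is a cheap improvement worth making, not a correction of an error.

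**What to change.** State the overall one-sided level for the primary family (0.025, if that is what is meant) and the success rule. Then replace the flat threshold by the matching procedure:

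- **Either endpoint is enough:** Holm at one-sided 0.025. Compare the smaller of the TAC and HDD p-values with 0.0125 and, if it is significant, compare the larger with 0.025.
- **Both endpoints are needed:** test each at one-sided 0.025 and claim success only if both are significant.

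The sample-size calculation can stay at 0.0125 as the conservative case. The change takes a sentence or two and needs no added patients or data. Under Holm, the plan should also say how confidence bounds will be reported when only one endpoint is significant.

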Although some research has indicated that tDCS may be effective in AUD and other substance-use disorders, these conclusions are preliminary, mainly because these studies are limited by small sample sizes. Thus, we aim to conduct an RCT with a large sample size to investigate whether or not a tDCS treatment strategy has the potential to become a promising treatment in AUD, in particular by determining whether tDCS has long-lasting effects in patients with AUD. Indeed, Klauss et al. found a lower rate of relapse at 6 months in patients with AUD treated with tDCS, but their study included only 33 participants, and the follow-up was based on information gathered by self-reports or reports of family members through visits and by telephone calls [12]. We hope that our study will remedy these shortcomings and provide a high level of evidence of the short and long-term efficacy of modulating DLPFC excitability via tDCS to treat AUD. This trial, which is one of the largest RCTs to assess the efficacy of tDCS in substance-related and addictive disorders, may also shed light on whether noninvasive brain stimulation techniques are of interest in the comprehensive treatment of addiction.

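### Each of 23 secondary outcomes may be called significant at the full one-sided 0.025, and week-24 TAC and HDD fall under two thresholds

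*Protocol article*

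**What the plan says.** The Statistical analysis section sets three rules. On direction: "All tests will be one-sided". On the primaries: "The primary results will be examined at a significance level of 0.0125 (co-primary outcome"). On everything else: "For secondary outcomes, the threshold for significance will be fixed at 0.025".

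The Outcomes section defines the secondary family in two lists. The first opens: "The secondary evaluation criteria will be the change from baseline to the end of the tDCS cessions and, then, for each 4-week period". Its schedule runs "for each 4-week period after the treatment up to week 24 in the following parameters", and TAC and HDD head the list. The second list (biochemical markers, cognition and tobacco measures) is assessed at weeks 4, 12 and 24.

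Continuous secondary outcomes are to be analysed with models similar to the primary one, and binary ones by logistic regression. The fixed effects named for the primary model are site, sex, time and treatment.

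The Discussion expresses the hope that the trial will "provide a high level of evidence of the short and long-term efficacy of modulating DLPFC excitability via tDCS to treat AUD".

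**The concern.** The plan controls multiplicity for two tests and then applies the whole one-sided alpha to each member of a much larger family, at a looser level than either primary receives. The word *significance* is attached to that level without any statement that the results are only supportive. If the primary analysis is negative, one or more secondary outcomes could still meet the article's threshold by chance and be reported as a significant benefit.

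There is also an inconsistency inside the article. The last 4-week period in the first secondary list ends at week 24. TAC and HDD in that period are the primary outcomes as the Outcomes section defines them, so the same comparison carries two thresholds.

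**Working it through.** **1. The plan's own alpha.** Two primaries at 0.0125: 2 × 0.0125 = 0.025 one-sided. This reproduces the total, and the same 0.025 then applies undivided to the secondary outcomes. The article states no family-wise error rate for them.

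**2. Count of secondary outcomes (Outcomes section).**
- First list: TAC and HDD (2), WHO risk shift (1), 50%, 70% and 90% reduction and abstinence (4), dependence scale (1), two craving scales (2), clinical global impression severity and improvement (2), depression score (1), SF-12 (1). Total 14.
- Second list: five biochemical markers, one cognitive score, three tobacco measures. Total 9.
- Sum: 14 + 9 = 23. Scoring the SF-12 as two components would make it 24.

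**3. Count of comparisons if each time point is tested.** The first list has seven time points (end of stimulation plus six 4-week periods) and the second has three: 14 × 7 + 9 × 3 = 98 + 27 = 125. Without TAC and HDD at week 24 it is 123.

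**4. Chance of at least one false benefit, one test per outcome.** With no effect on any outcome and k independent tests, the chance is 1 − (1 − 0.025)^k. For k = 23: 1 − 0.975^23 = 0.441.

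With a common correlation ρ between test statistics, it is 1 − ∫ φ(u) Φ[(1.96 − √ρ·u)/√(1 − ρ)]^23 du. The article gives no correlation between outcomes, so ρ is an assumption:

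| ρ | 0 | 0.3 | 0.5 | 0.7 | 0.9 |
|---|---|---|---|---|---|
| chance | 44% | 30% | 23% | 15% | 8% |

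Against the nominal 2.5%, that is 0.441/0.025 ≈ 18 times at ρ = 0, 0.225/0.025 = 9 times at 0.5, and 0.080/0.025 ≈ 3 times at 0.9.

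**5. The same chance with all 125 comparisons.** By simulation, taking 0.7 between time points of one outcome. The 0.7 is borrowed from the autocorrelation that the Sample size calculation section assumes for TAC; applying it to the other outcomes is an assumption.

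| Between-outcome correlation | 0 | 0.3 | 0.5 |
|---|---|---|---|
| same at all pairs of times | 84% | 56% | 41% |
| weaker between different times | 84% | 62% | 49% |

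If related outcomes form domains (assumed 0.6 to 0.8 within a domain, 0.1 to 0.3 between), the figures are about 23% to 29% for 23 tests and 49% to 59% for 125.

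**6. The double threshold.** Take a one-sided p of 0.02 for TAC in the final 28 days. As primary: 0.02 > 0.0125, not significant. As secondary: 0.02 < 0.025, significant. Any p between 0.0125 and 0.025 gives this contradiction.

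**The case against.** A reader might go further and infer that a false secondary benefit is *likely*. The documents do not support that. With one test per outcome the ceiling is 44%, and it requires independence. That is implausible when TAC, HDD, the WHO shift, the responder rates and abstinence all come from the same drinking record. The figure passes one half only if every time point is tested and the outcomes are not too strongly correlated.

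Nor is 125 tests the stated plan. The Outcomes section defines the criteria per period, which supports that count. But the model names no treatment-by-time term, which points to one treatment test per continuous outcome.

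Two further inferences should be resisted:
- The Discussion voices a hope for strong short-term evidence; it does not set an inferential rule. It also cannot be said that only secondary tests could supply such evidence, because the primary repeated-measures model, as written, draws on early periods too.
- Nothing in the article says that a secondary result may rescue a failed primary. Efficacy is tied to the principal criteria, and only these drive the sample size.

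Unadjusted secondary tests are common and acceptable when labelled supportive, and an analysis plan not shown here could add a hierarchy. Its absence from a condensed article is therefore no finding in itself. What remains is what the article does state: one undivided significance threshold for all secondary outcomes, and a family that overlaps the primary. A hierarchy elsewhere would have to override that sentence.

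**Conclusion.** The point holds at moderate size. The article sets a significance rule of one-sided 0.025 for each of 23 secondary outcomes. Under no effect, this gives about a 23% to 44% chance of at least one falsely significant benefit with one test per outcome, for assumed correlations from 0.5 down to 0. At an assumed 0.9 it is still about 8%, or three times nominal. If each time point is tested, the range is about 40% to 84%, conditional on that reading and on 0.7 over time. No correlation examined brings the rate near 2.5%.

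The double threshold for week-24 TAC and HDD needs no correlation assumption; it follows from setting the two sections side by side. The type I error of the primary analysis is unaffected. What is at stake is what may be concluded from the secondary results, so the change should be made, but the trial's main conclusion does not depend on it.

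**What to change.** In the Statistical analysis section, replace the sentence that sets 0.025 with: *Secondary outcomes are supportive and exploratory, reported as estimates with 95% confidence intervals and nominal p-values; no efficacy claim rests on them.*

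In the Outcomes section, take TAC and HDD at week 24 out of the secondary list, so that they are judged only at 0.0125.

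If a confirmatory short-term claim is wanted, name one secondary outcome and time point (for example TAC in the first 4-week period) and test it only after the primary succeeds. Leave the rest exploratory, and word the Discussion's hope for short-term evidence to match.

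The cost is wording in the protocol or analysis plan; it needs no patients, visits or data. The downside is that isolated secondary p-values below 0.025 can no longer be called significant.
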